#### Visit 0: Screening

Written informed consentDetailed screeningInvestigational screeningMedical history and examinationReview of inclusion and exclusion criteria

#### Visit 1: Baseline (0 Day)

Subjects found suitable for the study shall be enrolled.Medicine will be dispensed along with the drug compliance form.Instruction will be given to come on the next follow-up on the stipulated date.History of any sign and symptoms of pre-eclampsia,Weight,BP—right arm sittingUrine albumin/sugar

#### Successive visits

The subsequent follow-up will be for 24–28 weeks. After enrolment (visit 1), participants will be followed up at 20 weeks (visit 2) and 4 weekly till 28 weeks, i.e., at 24 weeks (visit 3) and at 28 weeks (visit 4). After 28 weeks period of gestation, the patient will be called two-weekly till 36 weeks, i.e., 30 weeks (visit 5), 32 weeks (visit 6), 34 weeks (visit 7), 36 weeks (visit 8). Participant will be called weekly after 36 weeks, i.e., 37 weeks (visit 9), 38 weeks (visit 10), 39 weeks (visit 11), and 40 weeks (visit 12).

#### Visits 2–12

Medicine will be dispensed along with the drug compliance form.Instruction will be given to come on next follow up on stipulated date.History of any sign and symptoms of preeclampsiaWeightBP—right arm sittingUrine albumin/sugar

Subjects will visit the investigating site 12 times during the trial or if participant is not able to visit; senior research fellow recruited in the project will visit her at her residence.

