##### Study interventions (investigational products)

Group A: will receive 75 mg of aspirin at night with water starting 12–16 weeks till completed 37 weeks or earlier if onset of preterm PE.

Group B: will receive150 mg of aspirin at night with water starting 12–16 weeks till completed 37 weeks or earlier if onset of preterm PE.

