#### Method of administration of investigational products

Every patient will be instructed to take one capsule at bed time starting from the time of enrolment. Aspirin will be stopped in both groups if a woman develops preterm PE, otherwise will be continued until completed at 37 weeks.

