### Comparison

Primary objective will be to compare 75 mg versus 150 mg aspirin for the prevention of preterm preeclampsia in screen-positive high-risk women. Secondary objectives will be to evaluate fetomaternal outcomes in high-risk women receiving 75 mg versus 150 mg aspirin for the prevention of preterm preeclampsia. Participants will be followed and onset of preterm PE < 37 weeks will be recorded. In case the women develop preterm PE, the aspirin will be stopped. All participants developing PE and not developing PE women will be followed till delivery and fetomaternal outcome will be noted.

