#### Study procedure

All screen-positive women fulfilling the criteria will be enrolled at 12–16 weeks of pregnancy after signing the consent form. The required baseline investigations will be carried out and that day will be visit 1 or baseline. Previous obstetric history, pre-pregnancy weight, and past history of preeclampsia will be recorded. Weight and height will be recorded. Blood pressure will be measured on the right arm in a sitting position, and urine albumin/sugar test will be performed. After enrolment, the women will be randomized to receive 75 mg or 150 mg aspirin at night from 12 to 16 weeks of pregnancy. The drug will be dispensed to her after fulfilling all the formalities as per the protocol.

The subsequent follow-up will be at 20 weeks (visit 2), and four-weekly till 28 weeks, i.e., at 24 weeks (visit 3) and at 28 weeks (visit 4). After 28-week period of gestation, participants will be called two-weekly till 36 weeks, i.e., 30 weeks (visit 5), 32 weeks (visit 6), 34 weeks (visit7), and 36 weeks (visit 8). Participant will be called weekly after 36 weeks, i.e., 37 weeks (visit 9). Aspirin will be stopped at 37 weeks or earlier to 37 weeks if onset of preterm preeclampsia. If they do not develop PE, then they will be called weekly at 38 weeks (visit 10), 39 weeks (visit 11), and 40 weeks (visit 12). Subjects will visit the investigating site 12 times during the trial or if participant is not able to visit; a senior research fellow recruited in the project will visit her at her residence..Participants will be followed and whether they have onset of preterm PE < 37 weeks will be recorded. In case the women develop PE, the aspirin will be stopped. All participants developing PE and not developing PE women will be followed till delivery and fetomaternal outcome will be noted.

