#### Treatment period

It will be 21–25 weeks in both groups. Study participant will be recruited at 12–16 weeks. The subsequent follow-up will be at 20 weeks (visit 2) and four-weekly till 28 weeks, i.e., at 24 weeks (visit 3) and at 28 weeks (visit 4). After 28-week period of gestation, the participants will be called biweekly till 36 weeks, i.e., 30 weeks (visit 5), 32 weeks (visit 6), 34 weeks (visit7), and 36 weeks (visit 8). Participants will be called weekly after 36 weeks, i.e., 37 weeks (visit 9), 38 weeks (visit 10), 39 weeks (visit 11), and 40 weeks (visit 12). Onset of preterm PE will be recorded, aspirin will be stopped, and participants will be followed till delivery and fetomaternal outcome will be noted. In participants who do not develop preterm PE, aspirin therapy will be stopped at 37 completed weeks and will be allowed to go till 40 weeks (term) if no obstetrical indication for induction and fetomaternal outcome will be recorded. At every visit, history will be taken and they will be asked for any signs and symptoms of preeclampsia; weight and BP will be measured and urine albumin test will be done Fig. 1.

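### The visit checklist hands out study medicine at 38, 39 and 40 weeks, after the point at which the protocol stops aspirin

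*Protocol article*

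**What the plan says.** The section *Visits 2–12* sets out a single list of procedures for all eleven visits. It opens with "Medicine will be dispensed along with the drug compliance form" and makes no exception by visit number, gestational age or PE status.

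The timing of the last visits is in *Successive visits*: "37 weeks (visit 9), 38 weeks (visit 10), 39 weeks (visit 11), and 40 weeks (visit 12"). *Study procedure* and *Treatment period* give the same weeks.

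The stop rule appears in four places:

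- *Study interventions*, for the lower-dose group: "75 mg of aspirin at night with water starting 12–16 weeks till completed 37 weeks or earlier if onset of preterm PE". The higher-dose group has the same limits.
- *Method of administration of investigational products*: "Aspirin will be stopped in both groups if a woman develops preterm PE, otherwise will be continued until completed at 37 weeks".
- *Study procedure*: "Aspirin will be stopped at 37 weeks or earlier to 37 weeks if onset of preterm preeclampsia".
- *Treatment period*, which ends aspirin at 37 completed weeks in women without preterm PE and gives the duration as "It will be 21–25 weeks in both groups".

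Follow-up outlasts treatment. Under *Comparison*, "All participants developing PE and not developing PE women will be followed till delivery".

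**The concern.** A visit checklist is the kind of text that staff work from when they hand out drug. This one tells them to dispense at three visits that lie after the last permitted dose. A woman given capsules at 38 weeks may reasonably take them.

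Two things are at stake. The first is exposure: aspirin would be supplied in the weeks nearest delivery, in both arms, in a trial that lists postpartum hemorrhage and hematoma formation among its outcomes. The second is an inference about the compliance record. Drug issued after the stop and correctly left untaken would come back as unused, and could look like missed doses in a trial that applies an 80% compliance threshold.

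**Working it through.** **Inputs**

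| Item | Value | Section |
|---|---|---|
| Start of aspirin | 12–16 weeks | *Study interventions* |
| Stop of aspirin | 37 weeks, or onset of preterm PE | *Study interventions*, *Method of administration*, *Study procedure*, *Treatment period* |
| Visits 2–8 | 20, 24, 28, 30, 32, 34, 36 weeks | *Successive visits* |
| Visit 9 | 37 weeks | *Successive visits* |
| Visits 10–12 | 38, 39, 40 weeks | *Successive visits* |
| Dispensing | every visit from 2 to 12 | *Visits 2–12* |

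**Step 1: reproduce the plan's own durations.** Duration = end week − start week.

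- Treatment: 37 − 16 = 21 and 37 − 12 = 25 weeks. This matches the stated 21–25 weeks.
- Follow-up: 40 − 16 = 24 and 40 − 12 = 28 weeks. This matches the 24–28 weeks in *Successive visits*.

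The plan's own figures thus separate a treatment phase that ends at 37 weeks from follow-up that runs to 40.

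**Step 2: place the visits against the stop.**

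- Before 37 weeks: visits 2–8, 7 visits, consistent with dispensing.
- At 37 weeks: visit 9, 1 visit.
- After 37 weeks: visits 10–12, 3 visits.
- Total: 7 + 1 + 3 = 11. Share after the stop: 3/11 = 27% of the visits under the list.

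**Step 3: does the result depend on what 37 weeks means?** The latest reading is 37+6. Visit 10, at 38 weeks, still comes after it. The conflict at visits 10–12 holds on either reading.

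**Step 4: can the treatment period settle visit 9?** If starts are exactly 12+0 and 16+0, a stop at 37+0 gives 21–25 weeks. If starts run to 12+6 and 16+6 and the stop is 37+6, then 37+6 − 16+6 = 21 weeks and 37+6 − 12+6 = 25 weeks, the same range. Starts are given in whole weeks only, so the range does not tell the two readings apart, and visit 9 is left out of the count.

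**Step 5: look for an exemption.** Neither the *Visits 2–12* list nor the sections next to it on visits, drug accountability and drug compliance says that dispensing ends at 37 weeks. *Study procedure at follow-up* has home visits maintain the supply of study drug, also without an end point.

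**The case against.** The strongest reply is that no site would be misled. The stop is stated four times, and *Study procedure* places it in sequence: visit 9 at 37 weeks, then the stop, then visits 10–12. The checklist is plainly generic. It also tells staff to give instructions for the next follow-up, which cannot apply at visit 12, the last scheduled one. Drug comes in bottles for a set number of weeks, unused drug is returned, and dispensing is recorded. Figures 1 and 2 are not shown and may mark dispensing by visit. The article also condenses a fuller protocol.

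Much of this stands. It makes the intended rule clear and sustained over-supply unlikely, which is why the point ranks low. It does not remove the conflict. None of those safeguards says that dispensing ends at 37 weeks. Whatever the figures show, this text would still read as it does. And the point is not that detail is missing, but that one stated instruction contradicts another.

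Three stronger readings are tempting, and the documents do not support them.

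- A reader might take the 21–25 weeks as proof of a stop at 37+0 and so count visit 9 as a fourth conflict. Step 4 shows that the range fits 37+6 equally well.
- A reader might infer that women already stopped for preterm PE would be given drug at 38–40 weeks. *Study procedure* calls women to those visits only if they have not developed PE: "they will be called weekly at 38 weeks (visit 10), 39 weeks (visit 11), and 40 weeks (visit 12"). Women with PE do stay in follow-up until delivery, but nothing says that they follow this checklist. The missing exception is worth closing; it does not show that they would be dosed.
- A reader might use the Introduction's bleeding rates in aspirin users and nonusers (for example postpartum hemorrhage, 10.2% against 7.8%) to size the harm. Those figures do not isolate dosing after 37 weeks.

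**Conclusion.** The contradiction is real and narrow. Three of the eleven visits under the checklist, those at 38, 39 and 40 weeks, call for dispensing after aspirin should have ended. This rests only on the visit weeks and the stop rule as printed, and on reading the list as applying to every visit in its heading.

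The 3 of 11 counts scheduled visits. It does not measure exposure: women who deliver earlier never reach those visits, and no quantity per visit is given. Any added bleeding risk cannot be quantified from the documents.

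The primary outcome is PE with onset before 37 weeks, so drug handed out at 38 weeks or later cannot change it, and the sample size does not depend on it. This is a low-priority correction to an operational instruction, worth making because it bears on safety near delivery and on clean compliance counts.

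**What to change.** Split the *Visits 2–12* list by phase:

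- **Up to visit 8 (36 weeks):** dispense, unless aspirin has already been stopped for preterm PE. The visit 8 supply should cover the nights up to 37 weeks.
- **Visit 9 (37 weeks), or the visit at PE onset if earlier:** collect and count the remaining drug; do not dispense.
- **Visits 10–12 (38–40 weeks):** history, weight, blood pressure and urine test only, without dispensing. Apply the same limit to home visits that replace them.

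The cost is a change of wording in the visit list and in the site's dispensing instruction. The treatment period stays at 21–25 weeks, and design, sample size and analysis do not change.

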#### Standard management of any ailment arises during the study trail period

Participants registered under the trial will be instructed to avoid the use of any other drugs on their own for any ailment and will be clearly instructed to consult the treating investigator for any symptom or complaint or if they feel anything unusual. The investigator will record any medication(s) she may prescribe to alleviate their ailments. To alleviate any emergency, the use of any medication is permitted as per the discretion of the investigator. However, the same needs to be documented in the appropriate column in the case report form (CRF).

#### Drug accountability

The study drug aspirin will be kept in a secure place and will only be supplied to patients in the study under the responsibility of the investigator. A record will be kept of the study drugs dispensed. Any discrepancies between amounts dispensed and returned will be explained. Study subjects will be encouraged to maintain the count of the medication dispensed to them.

#### Drug compliance

If there is more than or equal to 80% compliance, the participant would be continued in the trial. The compliance will be assessed at each visit during the follow-up (interval depending on POG) by assessing the approximate quantity of medicines consumed by the patient. The participant will be asked to return the empty container of medicine at the time of each follow-up visit. Repeated reminders will be given over the phone or through family members and project staff for regular taking of medicine.

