### Regular monitoring and follow-up

◦ Scheduled visits: participants will attend regular follow-up visits to evaluate adherence and address any issues. During these visits, adherence will be assessed through communication and review of medication logs.◦ Tablet return: participants will be asked to return unused medication at each visit. This will help researchers track missed doses and assess adherence rates.◦ Laboratory tests: periodic laboratory tests will be conducted to monitor physiological changes or side effects related to the intervention.

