### Withdrawal criteria

A participant if failed to adhere more than 80% to the requirements of aspirin intake and withdrew consent prior to the completion of the study.Every subject will be free to withdraw from the trial at any point in time for any reason.

The reason for withdrawal will be recorded in the CRF, dated, and signed. Efforts will be made to ascertain the reason for discontinuation.

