#### Assessment of drug compliance

The compliance of intake of IP will be monitored by assessing the approximate quantity of medicines consumed by the participants (minimum 80%). For this purpose, the participants will be instructed to return the empty container of the medicine at the time of each follow-up visit. Repeated reminders will be given over the phone or through family members by the project staff for regular intake of the medicine.

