#### Handling missing data

Strategies for handling missing dataData collection: to minimize missing data, we will implement thorough data collection procedures and follow up regularly with participants. Data checks and reminders will be employed to reduce missing data incidents.Imputation methods:▪ Multiple imputation: missing data will be addressed using multiple imputation techniques. This involves generating several imputed datasets to account for missing values, analyzing each dataset separately, and then combining the results to reflect the uncertainty due to missing data. This method assumes data are missing at random (MAR).▪ Last observation carried forward (LOCF): for missing data due to non-response at specific time points, LOCF may be used as a supplementary approach, assuming the last observed value is valid in the absence of further data.Model-based approaches:▪ Mixed-effects models: mixed-effects models will be used to handle missing data by accounting for both fixed and random effects, providing robust estimates despite incomplete data.▪ Maximum likelihood estimation (MLE): MLE will be employed to estimate model parameters, incorporating missing data directly into the estimation process under the assumption of data being missing at random.Sensitivity analysis: sensitivity analyses will evaluate the impact of different missing data handling methods on study results, assessing the robustness of findings under various assumptions about the missing data.Analysis of non-adherence to interventionaAnalysis of participants who do not adhere:Intention-to-treat analysis: participants will be analyzed according to their randomization assignment regardless of adherence. This approach maintains the benefit of randomization and provides an unbiased estimate of treatment effects.Per-protocol analysis: a per-protocol analysis will be performed for participants who adhere to the intervention as prescribed, assessing the effectiveness under optimal conditions.Compliance analysis:▪ Adherence rates: descriptive statistics will be used to calculate and characterize adherence rates.▪ Effectiveness among adherers: subgroup analyses will evaluate the effectiveness of the intervention among participants who follow the prescribed treatment.Instrumental variable analysis: if applicable, instrumental variable analysis may be used to address non-adherence issues by using variables correlated with adherence but not directly with the outcome.Imputation clarificationaImputation procedures:Multiple imputation approach:▪ Creating multiple imputed datasets: several datasets with imputed values will be created based on observed data and assumptions about missing data mechanisms.▪ Analysis of each dataset: each imputed dataset will be analyzed separately using the chosen statistical models.▪ Combining results: results from each imputed dataset will be combined using Rubin’s rules, accounting for within-imputation and between-imputation variability.Assumptions and validation: the assumptions behind the imputation methods will be validated, and sensitivity analyses will test the robustness of results under different imputation scenarios.Reporting: the imputation methods and rationale will be clearly reported, including the extent of missing data and the impact of imputation on the findings.

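### The 80% compliance rule can be read as ending participation, which conflicts with intention-to-treat and with following every woman to delivery

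*Protocol article*

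**What the plan says.** Two sections of the protocol article link a woman's place in the trial to her capsule intake.

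- Drug compliance: "If there is more than or equal to 80% compliance, the participant would be continued in the trial". The check is made at each follow-up visit.
- Withdrawal criteria, first entry, which begins: "A participant if failed to adhere more than 80% to the requirements of aspirin intake". The same sentence then adds, joined by a plain conjunction, that consent was withdrawn before the study ended. The next sentence lets any woman leave at any time for any reason. For withdrawals, the section asks only that the reason be recorded.

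Other sections point the opposite way.

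- Handling missing data, on intention-to-treat: "participants will be analyzed according to their randomization assignment regardless of adherence". The same section plans a separate per-protocol analysis, an analysis among adherers and possibly an instrumental-variable analysis.
- Comparison: "All participants developing PE and not developing PE women will be followed till delivery". Study procedure repeats this.
- Addressing non-adherence: women who show signs of it are contacted and helped. Removal is not mentioned.

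No section says that a woman who falls below 80% stays in outcome follow-up.

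**The concern.** Drug compliance speaks of staying in the trial, not of staying on study drug. A coordinator who reads it next to Withdrawal criteria could reasonably close the record of a woman whose intake is below 80%. An intention-to-treat analysis needs her outcome, and so do the planned contrasts between all women and adherers. If her follow-up ends, the analysis set moves towards the per-protocol set through a selection made after randomisation.

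Few events are expected, so each lost one counts. At the planned 147 per group, the design proportions imply about 147 × 0.17 = 25 events on 75 mg and 147 × 0.065 = 10 on 150 mg. Delivery outcomes such as postpartum haemorrhage, which bear on the comparison of side effects, would be lost with them.

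**Working it through.** **1. The sections side by side.** Drug compliance gives a condition for continuing; its converse is that a woman below 80% is not continued. Withdrawal criteria supports that reading if low intake counts as a criterion of its own. If low intake and withdrawal of consent form one joint criterion, it adds nothing, because the next sentence already allows withdrawal for any reason. Either way Drug compliance stands alone and does not mention consent. Ending participation below 80% cannot be combined with following all participants to delivery, or with having the data that analysis as randomised requires.

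**2. The plan's own sample size.** Inputs from Sample size: p1 = 0.17, p2 = 0.065, mean 0.1175, z = 1.96 and 0.842, attrition 20%.

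n = [1.96·√(2 × 0.1175 × 0.8825) + 0.842·√(0.17 × 0.83 + 0.065 × 0.935)]² / 0.105²

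= [0.8926 + 0.3783]² / 0.011025 = 146.5, so 147 per group. The plan states 146.6 and 147. Then 294/0.8 = 367.5, against 370 stated (185 per group). The figure reproduces.

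**3. Power if women are removed.** Power = Φ{[0.105·√n − 0.8926] / 0.4493}, where 0.4493 = √(0.17 × 0.83 + 0.065 × 0.935). Removed women are taken to contribute no outcome. The removal rates are assumptions; the documents give none.

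| Situation | n per group | Power |
|---|---|---|
| All women followed | 185 | 88.3% |
| 20% lost, removals included | 185 × 0.8 = 148 | 80.4% |
| 20% lost, then 10% removed | 148 × 0.9 = 133.2 | 76.1% |
| 20% lost, then 20% removed | 148 × 0.8 = 118.4 | 71.1% |

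The first row ignores any dilution of the effect by poor intake.

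**4. When removal would bias the comparison.** Let a share r of an arm be removed, and let removed women have k times the risk of retained women. If the whole arm has risk p, the risk among retained women is p/(r·k + 1 − r). Take no true dose difference, p = 0.1175 in both arms, with r and k assumed:

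- r = 10% in both arms: difference 0 for every k.
- r = 10% on 75 mg and 20% on 150 mg, k = 1: difference 0.
- Same r, k = 2: 0.1175/1.1 − 0.1175/1.2 = 0.1068 − 0.0979 = 0.9 percentage points.
- r = 10% and 30%, k = 3: 0.1175/1.2 − 0.1175/1.6 = 0.0979 − 0.0734 = 2.5 points.

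Bias therefore needs both unequal removal and a different risk in those removed. The last case is extreme and compares with a planned difference of 10.5 points. The direction reverses if removal is heavier on 75 mg, or if removed women are at lower risk.

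**The case against.** The strongest reply is that the protocol never says outright that poor adherers are removed. Drug compliance states only the positive condition, Withdrawal criteria can be read as requiring withdrawal of consent as well, and nothing says that outcome collection stops. The plan to analyse women who do not adhere presupposes data on them, and home visits are provided for women who cannot attend. The intention-to-treat statement is itself sound, and multiple imputation with sensitivity analyses is planned.

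Much of this stands: removal is an inference, and the intent may well be to keep everyone. It does not remove the conflict, because no sentence tells staff to keep such women in follow-up and two sentences suggest otherwise. Imputation assumes data missing at random, which would be doubtful if removal depended on unrecorded tolerability or risk.

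A reader might infer three stronger points that the documents do not support.

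- *Every woman below 80% at any one visit is removed, so the rule empties the trial.* With eight on-drug checks (visits 2 to 9) and independent failure rates of 3%, 5% or 10% per check, 1 − (1 − q)^8 gives 22%, 34% or 57%. But the plan does not say whether the 80% applies per interval or cumulatively, the rates are assumed, and poor intake probably clusters within women. With a beta-binomial within-woman correlation of 0.5, also assumed, the same rates give 8%, 13% and 24%.
- *Missing outcomes will depend on dose.* The documents give no compliance rates by dose, and both arms take one matching blinded capsule. This is a possibility, not a result.
- *Compliance is measured in contradictory ways.* Assessment of drug compliance says "the participants will be instructed to return the empty container of the medicine", while Regular monitoring and follow-up says "participants will be asked to return unused medication at each visit". The two are compatible, and Drug accountability requires discrepancies between drug dispensed and returned to be explained. The looser wording is a secondary matter.

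**Conclusion.** The contradiction holds, and it lies in the rules for staying in the trial rather than in the intention-to-treat statement. Drug compliance and Withdrawal criteria, read as written, permit an exclusion after randomisation that other sections rule out. That conclusion rests on the text alone.

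The size is conditional. If removals stay inside the attrition allowance, the trial keeps its planned power; the losses calculated above arise only if removals come in addition. Bias is possible but not shown, and its direction cannot be stated from the documents. The point should be settled promptly: Trial status reports that screening began on 1 May 2024, and outcomes not collected may not be recoverable later.

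**What to change.** Reconcile Drug compliance and Withdrawal criteria with Addressing non-adherence, Comparison, Study procedure and Handling missing data by stating that:

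1. Compliance below 80% is recorded and supported, and never ends outcome follow-up.
2. Only withdrawal of consent to follow-up ends data collection. The clause in Withdrawal criteria that joins low intake to withdrawal of consent is reworded accordingly.
3. All randomised women are followed to delivery and analysed as randomised.
4. The 80% threshold serves only to define the per-protocol set, based on the returned-drug checks already planned under Adherence support, Regular monitoring and follow-up, and Drug accountability.

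Whether study drug continues in a woman below 80% is a separate clinical matter for the sponsor, and the text should keep it distinct from follow-up.

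The cost is a wording amendment and a staff briefing. The clinic and home visits needed are already planned, and the sample size does not change.
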